## 1. Study Protocol

### Aims Of The Project

**Aim 1:** To test whether community-based periodic treatment of children 6-23 months old with mebendazole will decrease rates of severe anemia and protein-energy malnutrition by at least 20%.

**Aim 2:** To determine whether young children infected with intestinal nematode infections exhibit a more pro-inflammatory response to nematode antigens (i.e. characteristic of T Helper 1 [Th1] cells) than age-matched uninfected children.

**Aim 3:** To test whether mebendazole treatment of infected children reverses this pro-inflammatory response.

**Aim 4:** To measure intestinal blood loss related to relatively light hookworm infection in young children, and whether intestinal blood loss is reduced after treatment with mebendazole.

**Aim 5:** To elucidate metabolic mechanisms that could explain the link between a pro-inflammatory cytokine response and anemia and protein-energy malnutrition. Specifically, we aim:

A) To determine whether newly infected children show defects in iron metabolism compared to age-matched uninfected children, in a manner consistent with mechanisms of the “anemia of chronic disease” (i.e. decreased iron absorption, decreased iron incorporation into erythrocytes, suppressed erythropoiesis, and/or shortened red cell life span);

B) To determine whether newly infected children catabolize protein at greater rates than age-matched uninfected children;

C) To determine whether newly infected children are more anorexic than age-matched uninfected children.

### Background And Preliminary Data

Malnutrition, measured as low weight-for-age, is one of the strongest known risk factors for child mortality in developing countries. Based on an analysis of data sets from several diverse geographic and socio-cultural locations, 25 and 50% of child deaths between the ages of 1 and 4 years were statistically attributable to malnutrition. Although the risks associated with severe malnutrition are highest, more deaths are attributable to mild-moderate malnutrition, because it is so common. The relative contribution of mild-moderate malnutrition is especially great in sub-Saharan Africa. Severe anemia may also contribute to mortality in children, especially when it coexists with respiratory illness. Both protein-energy malnutrition and anemia are also associated with behavioral alterations and delays in child development.

The causes of childhood malnutrition are multiple. Inadequate dietary intakes of calories and essential nutrients are a major cause, but infectious diseases contribute significantly to both anemia and poor growth. The role of *subclinical* infection as a cause of poor growth in young children was hypothesized long ago, but its importance in populations has been difficult to demonstrate. The hypothesized pathways are mediated by pro-inflammatory cytokines that suppress appetite, cause losses of protein, and raise resting energy expenditure. These processes have been best described in adults with chronic disease, but may be particularly important in young children in developing countries.

The role of subclinical infection or inflammation as a cause of anemia—the so-called anemia of chronic disease—is much better described. This too is mediated by cytokines, which

have been shown to inhibit erythropoietin secretion and block its action on the bone marrow. Iron deficiency is generally considered the predominant cause of anemia in children in developing countries, but the role of subclinical infection as a cause of anemia may be grossly underestimated.

The research we propose to carry out in rural Tanzania is designed to test the hypothesis that intestinal nematode infections in young children contribute significantly to protein-energy malnutrition and anemia through a cytokine-mediated inflammatory response. Geo-helminth infections may be the most common subclinical infection encountered by children in tropical environments. The global prevalence of helminth infections is very high—with 20-30% of the world's children affected. In Zanzibar infection with at least one of the intestinal nematodes (hookworm, *Trichuris trichiura*, or *Ascaris lumbricoides*) is nearly universal by the age of 3 years. The public health motivation for studying these infections is strong, as drugs for treatment are inexpensive and widely available. The biomedical motivation is also compelling, as they can be safely studied through randomized trials. Thus, we believe this research will provide practical guidance to public health programs and will test a novel model for elucidating the role of subclinical infection and inflammation as a cause of malnutrition and anemia in early childhood.

**Figure 1. Conceptual Framework**

[figure not shown]

The hypothesis that subclinical intestinal nematode infections may cause wasting malnutrition and the “anemia of chronic disease” in young children is supported by preliminary data from a randomized trial we recently completed in rural Zanzibar (Table 1). A community-based sample of 614 children 6-71 months of age was individually randomized to receive 3-monthly mebendazole (500 mg) or an identical placebo. Our aim was to define the preschool age range in which anthelmintic treatment may be beneficial to child growth and development, and our prior hypothesis was that mebendazole would improve growth and hemoglobin in preschoolers  $\geq 3$  years old. Contrary to our expectation, we found significant benefits from anthelmintic treatment in children  $<30$  months of age, in whom infection intensities were light but in whom incident infections were common. In this younger age group, mebendazole-treated children showed no improvement in iron status, and their levels of serum ferritin (both an iron storage protein and an acute phase protein) decreased by a large amount. Clinical morbidity symptoms were carefully monitored, and no deleterious effects of mebendazole treatment were observed in any age group. *P. falciparum* is holo-endemic in Zanzibar and clinical cases were treated when detected, but no malaria prevention program was implemented during the study period. The reductions in wasting malnutrition and moderate-severe anemia were large compared to other feasible public health interventions, and may be associated with improvements in child survival and development. However, the statistical significance of the changes was marginal, and the study needs to be repeated in a larger sample of children.

**Table 1. Effects of regular mebendazole treatment on rates of low hemoglobin and wasting malnutrition in Pemban children 6-29 months old**

|                             | Mebendazole group
(n=85) | Placebo group
(n=99) | Relative Risk
(95% confidence limits) |
|-----------------------------|-----------------------------|-------------------------|------------------------------------------|
| Prevalence rates (%) |                             |                         |                                          |
| Hemoglobin < 90 g/L         | 24.7                        | 36.8                    | 0.68 (0.43-1.07)                         |

Although chronic gastrointestinal (GI) infections typically stimulate marked Th2 responses characterized by IgE and eosinophilia, nothing is known of the characteristics and subsequent development of the acute primary responses in the very young. Studies in rodent models of GI nematode infections have shown that the nature of the cytokine response (Th1 or Th2) to a primary infection is influenced by the host genetic background and also by the dose of infective stages. In this latter study, in the *Trichuris muris* mouse model, a high infective dose of eggs stimulated a strongly Th2-polarized response whereas a light infection stimulated a strong Th1 response (>12-fold increase in IFN- $\gamma$ ). Repeated trickle infection in this murine model eventually led to an increased Th2 response. A switch from Th1 response on primary exposure to a Th2 response following repeated infection has also been shown with *Schistosoma mansoni* infections in baboons. Initial GI nematode infections in young humans will invariably be light and so it seems plausible that infants will make a significant proinflammatory response on first exposure and that this may modulate to a Th2 response with repeated exposure in the absence of treatment. Similar to the differences observed between different mouse strains, human populations also show a marked variation in predisposition to worm infections and host genetic effects on the immune response may similarly influence this. Thus the tendency to produce proinflammatory responses may vary markedly within the population.

Thus, a major focus of this study will be to assess, for the first time, the balance of worm-induced Th1- and Th2-associated cytokines in newly infected infants and how this is influenced by treatment. There is also emerging evidence that helminth (filarial) infections in mothers sensitize for parasite-specific immune responsiveness in neonates and that this involves both Th1 and Th2 cytokines, with the pro-inflammatory cytokine IFN- $\gamma$  prominent. On first exposure to infection, therefore, marked secondary responses may be induced. Whether GI nematode infections

have similar effects is unknown but in Pemba infection rates in women of child-bearing age are very high. In 1995 we conducted a community-based survey of 582 Pemban women of reproductive age, and found that 91% were infected with hookworms. For this reason we will assess maternal helminth infection rates as a potential covariate of infant immune response to infection.

## Experimental Design and Methods

We propose to conduct a community-based individually randomized trial of 3-monthly mebendazole treatment to assess the outcomes described in the framework and aims. The study area will be a geographically contiguous group of villages selected for the convenience of sample transport to the laboratory (within about 30 minutes drive by landrover). The PHL is currently conducting a complete population census of Pemba Island, which will allow us to define an area large enough to generate the needed sample size.

A representative sample of 2500 children ages 6-23 months will be screened for helminth infection. All 2500 children will be randomly allocated to treatment with a 3-day course of mebendazole, 100 mg twice daily, or identical placebo. This regimen was chosen to replicate the same drug used in our preliminary trial, but to maximize the efficacy of this drug against hookworms and *T. trichiura*. The study period will be 12 months duration, so that children have their first and final assessments in the same calendar month of the year, thus holding constant any seasonal effects. Anemia and PEM (**Aim 1**) will be assessed in the full sample.

To answer **Aims 2 & 3**, age-matched triplets of children will be selected according to their infection status at baseline. A triplet will be comprised of two infected and one uninfected child of similar age. The two infected children will be matched for species of infection. 250 matched triplets (total n=750) will comprise the Immunology Subsample. We chose 2:1 matching of infected to uninfected, because we are dealing with 3 species of infection and we want to increase our capacity to examine differences by species. Based on our preliminary data, a starting sample of 2500 children will be required to generate at least 500 infected cases. These children will be assessed for immunological parameters at baseline (prior to treatment) and again in the 10th month of the study, one month after the 4th (9-month) treatment round. The post-treatment time was chosen to maximize treatment effect by capturing all 4 rounds of treatment and by timing the assessment one month after the final treatment, when egg counts should be maximally reduced by the mebendazole.

To answer **Aim 4**, a subsample of 300 children will be constructed of hookworm-negative (n=100), light hookworm infections (1-999 epg, n=100) and moderate hookworm infections ( $\geq 1000$  epg, n=100). These classifications are lower than typically used in school children, and were chosen for children 6-24 month who have lighter infection intensities but whose total body iron store is limited or absent. Therefore small quantities of GI blood loss could have significantly alter their iron balance. Intestinal blood loss will be measured in this subsample at just prior to treatment, and 1 and 12 months post-treatment. This HemoQuant subsample will be drawn from the Immunology Subsample, so that immunologic data will also be available.

To answer **Aims 5A and 5B**, a subsample of 20 newly-infected and 20 uninfected (total n=40) children will be selected from the Immunology Subsample. This number, although small for an epidemiologic study, is large for a metabolic study involving stable isotopes. To our knowledge it is the largest sample size ever involved in a similar protocol. However, many factors may affect the metabolism of these children and it is essential to limit the heterogeneity within this sample to reduce variance unrelated to the factors of interest (i.e. helminth infection status and cytokine response). Thus, we will impose inclusion criteria based on age (12-23 months old), wasting malnutrition (weight-for-height Z scores  $\geq -1$ ), recent illness (no significant morbidity in the prior 2

weeks, and malaria infection (<1000 parasites/mL). Because these children will be drawn from the age-matched triplets defined for the Immunology study, the 20 children in the newly-infected group and the uninfected groups will be further matched on age within the 1-year-old age category.

**Specific Aim 5C** will be addressed using maternal reports of poor appetite, a method that is valid and very simple to implement. Therefore anorexia will be assessed in the full sample of 2500 children just prior to treatment and at 3, 6 and 12 months post-treatment.

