**Figure 2. Data collection schedule.**

| Study Month:                                    | 0 | 1 | 2 | 3 | 4 | 5 | 6 | 7 | 8 | 9 | 10 | 11 | 12 |
|-------------------------------------------------|---|---|---|---|---|---|---|---|---|---|----|----|----|
| FULL SAMPLE (n = 2500)                   |   |   |   |   |   |   |   |   |   |   |    |    |    |
| Fecal samples                                   | X |   |   |   |   |   |   |   |   |   |    |    | X  |
| Randomized Rx                                   | X |   |   | X |   |   | X |   |   | X |    |    | X  |
| Capillary blood                     | X |   |   | X |   |   | X |   |   | X |    |    | X  |
| Appetite                                        | X |   |   | X |   |   | X |   |   | X |    |    | X  |
| MUAC                                            | X |   |   | X |   |   | X |   |   | X |    |    | X  |
| Mother's milk                       | X |   |   |   |   |   |   |   |   |   |    |    |    |
| IMMUNOLOGY SUBSAMPLE (n=750) |   |   |   |   |   |   |   |   |   |   |    |    |    |
| Mother's fecal                                  | X |   |   |   |   |   |   |   |   |   | X  |    |    |
| Venous blood                        | X |   |   |   |   |   |   |   |   |   | X  |    |    |
| Anthropometry                                   | X |   |   |   |   |   |   |   |   |   | X  |    |    |
| HemoQuant                           | X |   |   |   |   |   |   |   |   |   | X  |    |    |

1) Capillary blood sample for determination of hemoglobin and malaria parasite density.

2) Only collected from mothers of children 6-12 months old.

3) Data collected in subsamples are in addition to the data collected for the full sample.

4) Venous blood sample will be used for assays of cytokine secretion in response to antigenic stimulation (whole blood assay), acute phase proteins, immunoglobulins, and iron status indicators.

5) HemoQuant assay will be performed on fecal samples collected for parasitology; no additional samples will be collected.

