At the 2-week pre-treatment visit, each infant will be given an oral dose of NaBr (1.5 g/kg) and  $^{57}\text{Fe}$  (7 mg, as ferrous sulfate). Infants will then be allowed to nurse and will be fed a standard meal 1 hour post-dosing. The majority of prior studies in infants have estimated red blood cell iron incorporation at 90% in infants. This assumption simplifies the studies and allows them to be done using only a single oral iron isotope. However, the degree of iron incorporation into red cells may be altered in these infants due to subclinical infections. We will therefore directly measure the degree of iron incorporation into red cells by administering a second intravenous iron isotope. An intravenous dose of  $^{58}\text{Fe}$  (0.6 mg as ferrous citrate) will be administered over 5 minutes. Blood volume assumptions are also necessary. Most studies estimate blood volume at 65-80 mL/kg. Information obtained from the deuterium (body composition study, see below) and NaBr tracer dosing will allow us to directly measure extracellular fluid volume and total body water and reduces the assumptions necessary for making calculations about iron metabolism. A venous blood sample will be taken 4 hours after the oral dosing to measure NaBr concentration.

At the treatment visit, a 5 mL blood sample will be drawn by venipuncture. One mL whole blood will be digested using ultrapure acids. Iron will be extracted using cation-exchange chromatography. The eluent will be dried and the iron residue will be dissolved in nitric acid. Iron isotope ratios will be determined using magnetic sector thermal ionization mass spectrometry (Finnigan MAT 261, Bremen, FRG). These methods have been previously described in detail.

Few data have addressed the impact of parasitic infections on the lifespan of erythrocytes in infants and the timing of maximal iron incorporation into red cells. Studies have indicated that the lifespan of the erythrocyte is markedly lower in infants than adults and a recent study has found alterations in the time course of iron incorporation into erythrocytes in infants. An additional blood sample is already planned at the 1 month post-treatment visit for immunology and protein turnover studies. We will also analyze the enrichment of iron isotopes in these blood samples to compare the stability of the tracer enrichments between infection and treatment groups.

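### The Aim 4 blood-loss schedule contradicts itself, and Figure 2 pairs no post-treatment HemoQuant mark with a child stool

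*Protocol*

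**What the plan says.** Aim 4 has two halves: how much blood young children lose with fairly light hookworm infection, and whether mebendazole lowers that loss. It is to be answered in 300 children (100 hookworm-negative, 100 light, 100 moderate) drawn from the Immunology Subsample of 750.

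The timing is given in these places:

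- Experimental Design and Methods, Aim 4 paragraph: "Intestinal blood loss will be measured in this subsample at just prior to treatment, and 1 and 12 months post-treatment".
- Figure 2, HemoQuant row: "HemoQuant 5 | X | | | | | | | | | | X", that is, months 0 and 10.
- Figure 2, footnote 5: "HemoQuant assay will be performed on fecal samples collected for parasitology; no additional samples will be collected".
- Figure 2, full-sample stool row: "Fecal samples | X | | | | | | | | | | | | X", that is, months 0 and 12. No other row collects stool from the child.
- Figure 2, Immunology Subsample: "Mother's fecal | X | | | | | | | | | | X". The stool marked at month 10 is the mother's.
- Figure 2, treatment row: rounds at months 0, 3, 6, 9 and 12.

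Two further passages bear on this. The Aims 2 and 3 paragraph places the immunology follow-up in month 10 and justifies it "by timing the assessment one month after the final treatment, when egg counts should be maximally reduced by the mebendazole". The iron metabolism text for the Metabolic Subsample states: "An additional blood sample is already planned at the 1 month post-treatment visit for immunology and protein turnover studies".

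**The concern.** The text and the figure give different months for the same measurement, and the footnote ties the assay to stool that the figure does not collect from the child at month 10. A field team working from Figure 2 would reach month 10 with an assay scheduled and no specimen, and month 12 with a specimen and no assay scheduled.

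At stake is the second half of Aim 4, whether treatment reduces blood loss. The Justification Of Sample Size section expects light infections in this age group and doubled the earlier group size, from 50 to 100, in order to detect smaller losses. With so small a signal expected, the time of measurement should not be left open. A stool that was not collected cannot be recovered at the analysis stage, so an analysis plan could not repair this.

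**Working it through.** No power formula applies, since the question is which months each passage allows. The Protocol gives no effect size, standard deviation or power for HemoQuant, so there is no stated figure to reproduce.

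**Step 1. Set the sources side by side.**

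| Source | Months |
|---|---|
| Aim 4 text, one-month time read as study month 1 | 0, 1, 12 |
| Aim 4 text, one-month time read as month 10 | 0, 10, 12 |
| Figure 2, HemoQuant row | 0, 10 |
| Figure 2, child stool row | 0, 12 |
| Figure 2, mother's stool row | 0, 10 |

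**Step 2. Compare the text with the HemoQuant row.** Under the month-1 reading they disagree at months 1, 10 and 12. Under the month-10 reading they disagree at month 12 only.

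**Step 3. Apply footnote 5, so that a HemoQuant value needs a child stool.**

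| Month | HemoQuant mark in Figure 2 | Child stool in Figure 2 | Months since preceding round |
|---|---|---|---|
| 0 | yes | yes | none before |
| 1 | no | no | 1 − 0 = 1 |
| 10 | yes | no | 10 − 9 = 1 |
| 12 | no | yes | 12 − 9 = 3 |

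The last column assumes that the month-12 stool is taken before the round marked for month 12. The only month with both a mark and a child stool is month 0. The number of post-treatment months with both is zero, for all 300 children.

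**Step 4. See what can be recovered.** Stool from month 12 is already to be collected in the full sample, so marking HemoQuant there gives a month 0 versus month 12 comparison. It falls three months after the preceding round. The month-10 immunology visit falls one month after, the interval chosen there so that the treatment effect would be largest.

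**Step 5. Check the related visit.** The iron metabolism text treats a one-month blood sample as already planned for both immunology and protein turnover. Figure 3 does schedule a metabolic visit one month after treatment, so the protein turnover part is covered. Immunology, however, is placed at months 0 and 10 by both the Aims 2 and 3 paragraph and Figure 2, so only the reference to immunology lacks a match.

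**The case against.** The best reply is that this is a drafting slip. A HemoQuant mark at month 10, on stool meant for parasitology, presupposes a child stool at that visit. The visit exists, with venous blood and anthropometry marked, and the mother's stool entry may be mislabelled or a child row may have dropped out. The immunology paragraph itself treats month 10 as the post-treatment time, so the Aim 4 text may mean month 10 as well. All of this is plausible, and it narrows the gap to one missing mark at month 12 and one missing stool at month 10. It does not close the gap. The Protocol nowhere says that the entry is a slip, its background gives a separate reason for examining mothers, and footnote 5 rules out extra samples.

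Several stronger readings are tempting but not supported:

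- A reader might infer three stated HemoQuant schedules. Only two are stated; months 0 and 12 follow by combining footnote 5 with the child stool row.
- A reader might infer that Aim 4's treatment question cannot be answered at all. The month-12 stool still permits a comparison.
- A reader might infer that reinfection will have diluted the effect by month 12. The Protocol gives no reinfection rate or time course of blood loss, and its one-month rationale concerns egg counts and the immunology assessment.
- A reader might use the metabolic schedule to rule out the month-10 reading. That schedule belongs to a separate 40-child subsample and does not settle what the Aim 4 sentence means.
- A reader might call the lack of a month-10 child egg count a defect for Aim 3. No passage promises one, and the randomized contrast does not depend on it; wanting one is a preference.

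**Conclusion.** The Aim 4 measurement schedule is wrong as written. On either reading of the one-month time, the Aim 4 text, the HemoQuant row, the child stool row and footnote 5 cannot all be followed. Taken literally, Figure 2 yields 0 post-treatment HemoQuant values for the 300 children, which defeats the treatment half of Aim 4.

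The damage is bounded. The baseline comparison across the three infection-intensity groups rests on month 0, which every source shares, and is unaffected. Aim 1 is untouched. A month 0 versus month 12 comparison is recoverable, at three months after the preceding round instead of one; whether and by how much this weakens the contrast cannot be derived from the Protocol.

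The conclusion assumes that Figure 2 is the complete collection schedule for these children and that footnote 5 means what it says. If the figure merely omits a child stool at month 10, the correction is smaller but still needed. The one-month immunology blood sample mentioned in the metabolic section is a minor inconsistency alongside it.

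**What to change.** Reconcile the Aim 4 sentence, the HemoQuant row, the child stool row and footnote 5 into one schedule in which every HemoQuant time has a child stool.

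- State whether the one-month time means study month 1 or month 10. Month 1 would require a visit that Figure 2 does not show.
- Mark HemoQuant at month 12, where child stool is already collected. This adds an assay per child but no collection.
- If month 10 is kept, add a child stool row for the 300 HemoQuant children at the existing month-10 visit, and amend footnote 5 so that it no longer excludes additional samples.
- Reconcile the metabolic section's reference to an immunology blood sample at one month with the months 0 and 10 given in the Aims 2 and 3 paragraph and in Figure 2.

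The cost is a Protocol and Figure 2 amendment. If month 10 is kept, there is also one extra stool collection and assay per child at a visit that already takes place, up to 300 in all. The amendment should be made before fieldwork starts.

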### **Data Analysis**

Data will be entered using an Oracle-based data management system. Data analysis will be directed by [name], with full participation of the research team to interpret and publish findings. Primary analyses will compare relative risks (Aim 1) or means (Aims 2-5) between groups defined by pre-treatment infection status or treatment group, according to the specific aims.

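### Aim 5C promises an age-matched comparison, but the methods assign it to the full sample, which is not age-matched, and state no age control

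*Protocol*

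**What the plan says.** All places are in the Protocol.

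- **Aims Of The Project, Aim 5C** sets the comparison: "To determine whether newly infected children are more anorexic than age-matched uninfected children".
- **Experimental Design and Methods** takes the aims in turn and gives each its population. Aims 2 and 3 get the Immunology Subsample of 250 triplets (750 children): "A triplet will be comprised of two infected and one uninfected child of similar age". Aims 5A and 5B get 40 children from that subsample, and the matching is carried over expressly: "Because these children will be drawn from the age-matched triplets defined for the Immunology study". Aim 5C gets the whole cohort: "Therefore anorexia will be assessed in the full sample of 2500 children just prior to treatment", with repeat assessments at 3, 6 and 12 months afterwards.
- The whole cohort is described as follows: "A representative sample of 2500 children ages 6-23 months will be screened for helminth infection". No age matching is described for it.
- **Data Analysis** reads: "Primary analyses will compare relative risks (Aim 1) or means (Aims 2-5) between groups defined by pre-treatment infection status or treatment group". The sentence ends by referring to the specific aims. It names no age term.
- **Figure 2, note 3** says that subsample data are additional to full-sample data, so children in the triplets have appetite recorded too.

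**The concern.** The aim makes age part of the comparison, and the population named for it does not supply that. Pre-treatment infection status is not randomised, so randomisation cannot balance age between infected and uninfected children.

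An age imbalance is likely. The protocol counts on at least 500 infected among 2500 children aged 6-23 months, while Background says that nearly every Zanzibari child carries at least one of the three nematodes by age three. Infected children in this cohort are therefore plausibly older than uninfected ones. If mothers' reports of poor appetite also change with age over this period, a crude contrast would mix age with infection. It could suggest a link that does not exist or hide one that does.

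**Working it through.** The protocol gives no sample size, power or effect size for Aim 5C, so there is no stated figure to reproduce. The calculation shows how large an age effect could be in a crude full-sample contrast when infection has no true effect on appetite.

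**Inputs from the protocol**
- Full sample 2500, ages 6-23 months; at least 500 infected (Experimental Design and Methods). Taking 500 as the count, the infected share is p = 500/2500 = 0.20, leaving 2000 uninfected.
- Poor appetite 12.1% (Table 1, placebo group, ages 6-29 months). It is the nearest available rate and is not broken down by age or infection status.

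**Assumptions (not in the protocol)**
- Age uniform over the 18 months from 6 to 24, so its variance is 18²/12 = 27.
- Infection prevalence linear in age with mean 20%, rising from 10% to 30%, 5% to 35%, or 2% to 38%.
- Poor appetite linear in age with a gradient of 0.25, 0.5 or 1 percentage point per month, in either direction.

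**Step 1: age gap.** Mean age of infected minus uninfected = slope of prevalence × variance of age / [p(1 − p)], with p(1 − p) = 0.16.
- 10-30%: (0.20/18) × 27 / 0.16 = 1.88 months
- 5-35%: (0.30/18) × 27 / 0.16 = 2.81 months
- 2-38%: (0.36/18) × 27 / 0.16 = 3.38 months

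**Step 2: standard error of the crude difference.** √[0.121 × 0.879 × (1/500 + 1/2000)] = 0.0163, or 1.63 points.

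**Step 3: spurious difference** = gradient × age gap. The rejection rate is that of a nominal two-sided 5% test, Φ(−1.96 + z) + Φ(−1.96 − z), where z = spurious difference / SE.

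| Appetite gradient (points per month) | Spurious difference (points) | In SEs | Rejection rate with no true effect |
|---|---|---|---|
| 0 | 0 | 0 | 5% |
| 0.25 | 0.5-0.8 | 0.3-0.5 | 6-8% |
| 0.5 | 0.9-1.7 | 0.6-1.0 | 9-18% |
| 1 | 1.9-3.4 | 1.2-2.1 | 21-54% |

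The sign of the difference follows the sign of the gradient.

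**Cross-check on the relative-risk scale.** Using whole months 6 to 23, the same three prevalence patterns, and poor appetite running between 6.0% and 18.2% (rising or falling, mean 12.1%), the crude relative risk with no true effect is:
- 0.89 to 1.12 for 10-30%
- 0.83 to 1.18 for 5-35%
- 0.80 to 1.22 for 2-38%

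It is exactly 1.00 if either gradient is flat.

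**Does it matter which age-controlled comparison is used?** Matched triplets supply 500 infected and 250 uninfected children. At an assumed 10% versus 15% poor appetite (two-sided 5%, no attrition, groups treated as independent), power is about 47% with 500 versus 250 and about 87% with 500 versus 2000. Controlling age in the full sample starts from the larger of these; the second figure is for an unadjusted comparison.

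**The case against.** The strongest reply is that the sentence on Aim 5C concerns measurement. It says whose appetite is recorded and when, because maternal report is simple to collect, and it names no comparison groups. Data Analysis defers to the specific aims, and Aim 5C itself says age-matched. The triplets lie inside the full sample and have appetite data, so a matched contrast remains possible. Age adjustment could also be specified in an analysis plan that is not shown; the pilot's arm-circumference result was age-adjusted.

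Much of this stands. A reader might infer that the protocol commits to a crude, unmatched analysis, or that age is already mixed into the anorexia difference. The document supports neither. No sentence prescribes an unadjusted contrast, and no figures are given for infection by age within 6-23 months or for appetite by age. The 500 is also a minimum, used here as if it were the expected count.

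The mismatch survives. The sentence sits in a passage that gives each aim its population. Matching is carried expressly into Aims 5A and 5B, and the sample named for 5C lacks it. The closing reference to the aims in Data Analysis most naturally selects infection status or treatment group for each aim; it does not supply an age-matched comparator. Nothing in the protocol says how the comparison in Aim 5C is to be formed.

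**Conclusion.** The concern holds as a mismatch between an aim and its methods: the comparator is age-matched, the assigned sample is not, and no age control is stated for a contrast that randomisation does not protect. That part rests on the text alone.

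Confounding is a possibility, not a demonstrated fact. It requires infection to rise with age within the cohort, which is very plausible, and reported appetite to vary with age, which the protocol does not address. The illustrative 0.5 to 3.4 points depends wholly on the assumed gradients; the true bias may have either sign or be zero.

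The point is limited to the infection-status contrast in Aim 5C. The comparison of appetite between randomised mebendazole and placebo groups is not affected.

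**What to change.** In the Aim 5C paragraph of Experimental Design and Methods, or in Data Analysis, state that the infection-status contrast for poor appetite is made in the full sample conditional on age in months, either by adjustment or by stratification in narrow age bands. Name the within-triplet comparison in the Immunology Subsample as a check. Settling this in advance also prevents a choice, after the data are seen, between two analyses that differ in power and in exposure to age confounding.

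The cost is a sentence or two of analysis wording. Age should be known for every child, since eligibility and triplet matching depend on it, and no sample size, visit or measurement changes.
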